### Interim analysis and early stopping rules

An early stopping rule will be applied when there is complete rotator cuff re-tears corresponding to at least 25% of the calculated number in the PR group as verified by ultrasonography 6 weeks postoperatively, provided that the re-tear rate is more than twice as high compared to that in the control UC group [79]. The trial steering committee (the authors of this manuscript) decide if the early stopping rule should be effectuated.

### Safety monitoring

No data monitoring committee has been established since adverse events are expected to be minimal and the intervention is not considered to be high risk. The physiotherapists at each center will report any adverse event to the primary investigator, who reports these to the ethics committee. The person responsible for randomization will monitor if the number of adverse events has reached the threshold for the early stopping rule. Further, if a patient experiences extreme worsening of symptoms during exercise therapy and these symptoms have not subsided before the next exercise session, the physiotherapist will report it to the primary investigator, who may refer the patient to an orthopedic specialist for an evaluation. The number and seriousness of AEs will be reported.

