**Fig. 1 Fig1:**
[figure not shown]
Expected flow of patients through the study. PR, progressive rehabilitation; UC, usual care

The second phase includes the secondary endpoint 52 weeks after baseline, at which point Ultrasound (US) measurements are included in the outcome assessments. During the 40-week follow up period (from week 12 to week 52) most patients continue standard rehabilitation in the community for 4–8 weeks. The community care providers are not informed about initial treatment to which each patient has been allocated (unless the patients tell them) and can thus be considered quasi-blinded.

After 12 weeks no study-related activities are performed, except for the 12-month follow up and treatment of any adverse events that might occur during the trial (52 weeks). Patients are randomized equally (1:1) to receive either PR or UC (Fig. 1).

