### Interventions

Patients in both treatment groups have the affected shoulder immobilized in a fixed sling for 2 weeks followed by 3 weeks in a non-fixed sling. The PR group starts loading (assisted active range of motion (AAROM) and active range of motion (AROM)) from week 2, while this is introduced in the UC group from week 6. The PR group is attending individual physiotherapist-supervised exercise therapy three times weekly, supplemented with daily home exercises (week 2, 3, 4 and 5), and the UC group is attending individual physiotherapist-supervised exercise therapy once a week supplemented with daily home exercises (week 2, 3, 4 and 5). From weeks 6 to 12 all patients receive physiotherapist-supervised exercise therapy twice a week (individually or in small groups) next to the self-administered exercise once a week (Table 1). Descriptions of on-site and home interventions are found in the additional files (Additional files 1 and 2).

**Table 1 Tab1:** Overview of the postoperative intervention in main trial

Week	Progressive rehabilitation (PR)	Week	Usual care (UC)
1- 5	Shoulder immobilized in standard sling.	1- 5	Shoulder immobilized in standard sling.
2- 5	Physiotherapist guided PROM exercises PROM Restrictions: ABD + FLEX: None IR < 90 degrees in neutral ER < 45 degrees in neutral	2- 5	Physiotherapist guided PROM exercises PROM Restrictions: ABD + FLEX: None IR < 90 degrees in neutral ER < 45 degrees in neutral
2	Close-chain AAROM and AROM exercises AAROM and AROM Restrictions: ABD + FLEX < 90 degrees IR < 90 degrees in neutral ER = 0 degrees in neutral		
3- 5	Close-chain AAROM and AROM exercises AAROM and AROM Restrictions: ABD + FLEX < 90 degrees IR < 90 degrees in neutral ER < 45 degrees in neutral		
6-12	Therapist-supervised AROM (FLEX, ABD, EXT, ER and IR) with gradually (individually) increased loading and progression from close-chain to open-chain exercises.	6-12	Therapist-supervised AROM (FLEX, ABD, EXT, ER and IR) with gradually (individually) increased loading and progression from close-chain to open-chain exercises.
12-20	Continuation of rehabilitation in the community	12-20	Continuation of rehabilitation in the community

*PR* progressive rehabilitation, *UC* usual care, *ROM* range of motion, *PROM* passive range of motion, *ABD* abduction, *FLEX* flexion, *IR* Internal rotation, *ER* external rotation, *AAROM* assisted active range of motion, *AROM* active range of motion, *EXT* extension

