Thus, the US investigation at 12 months involves quantitative measures of the repaired and contralateral SST thickness and neovascularity (NV), in addition to the SAS measured as the acromiohumeral distance (AHD). Ultrasound images are captured with the patients seated in an upright position, feet flat on the floor, neutral trunk posture, and head facing forward. For the SST thickness measure the patient has the hand on the affected side on the ipsilateral posterior hip with the humerus in extension and the tendon is measured in a longitudinal [72] and a transverse view [67]. AHD is measured in the neutral position (arm resting at the side) and respectively with 45° and 60° of active shoulder elevation in the scapular plane [72, 73]. SST neovascularity assessed by power Doppler is measured with the shoulder internally rotated with the dorsal side of the hand placed on the sacrum, and the elbow flexed and directed laterally [74].

Registered demographic data include age, gender, tendon(s) involved, supplementary surgery performed, hand dominance, history of trauma, occupation/employment and preoperative sports/recreational activity level. Demographic data and baseline measures will be used in the analysis of predictors of health outcomes.The investigator or site personnel monitor each patient for adverse events (AEs) throughout the study. Tendon re-tear is assessed by US at 6 weeks postoperatively and any re-tear is recorded. The investigator assesses and records any AE (in response to a query, observed by site personnel or reported spontaneously by the patient) in detail, including the date of onset, description, severity, duration and outcome, relationship of the AE to study intervention and any action(s) taken. All AEs will be followed closely to make sure that the patient is safely handled including follow up on clinical issues, until a stable situation is reached.

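### Adverse event ascertainment is unequal by design in weeks 2 to 5 (12 against 4 supervised sessions), which can bias the comparison of transient, non-serious events against progressive rehabilitation

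*Protocol article*

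**What the plan says.** All references are to the protocol article.

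- **Reporting route.** Safety monitoring states: "The physiotherapists at each center will report any adverse event to the primary investigator". The investigator passes events on to the ethics committee, and AE counts and seriousness are to be published. Under Blinding, those who deliver the treatment know the allocation.
- **Second route.** Outcome measures/variables states: "The investigator or site personnel monitor each patient for adverse events (AEs) throughout the study". It accepts events that come up on questioning, that staff see, or that the patient volunteers.
- **Session schedule.** Under Interventions, for weeks 2 to 5: "The PR group is attending individual physiotherapist-supervised exercise therapy three times weekly". UC has one supervised session a week in those weeks. After that: "From weeks 6 to 12 all patients receive physiotherapist-supervised exercise therapy twice a week".
- **After the programme.** Methods/design states: "After 12 weeks no study-related activities are performed, except for the 12-month follow up and treatment of any adverse events" arising up to week 52. Rehabilitation continues with community providers.
- **Common visits.** Both arms are assessed at 6 weeks, 12 weeks and 12 months. Re-tear is checked by ultrasound at 6 weeks.
- **Use of the data.** The Statistical analysis plan section lists complications among the binary outcomes for logistic regression.

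**The concern.** The staff named in the safety section as AE reporters see one arm three times as often as the other. This happens in weeks 2 to 5, the only weeks in which the two programmes differ and therefore the weeks in which a safety difference is of most interest. A brief event, such as a pain flare that settles in a few days, has more chances of being noted in PR than in UC even if it is equally frequent in both. The reporters are also unblinded.

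The text describes no outcome visit between baseline and week 6, so the supervised sessions are the only in-person contacts with trial staff that it describes for weeks 2 to 5. Observation by staff, and the opportunity to volunteer a complaint face to face, then follow the same 12 to 4 pattern.

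At stake is the published AE comparison. If short, minor events appear more often in PR, a reader cannot tell how much of the excess comes from earlier loading and how much from closer watching. The trial has no data monitoring committee, so these tables carry much of the safety message.

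**Working it through.** The plan gives no figure to reproduce here. The check has two parts.

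**1. Contacts, from the Interventions schedule**

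| Period | PR | UC | Ratio |
|---|---|---|---|
| Weeks 2-5 | 3 × 4 = 12 | 1 × 4 = 4 | 3.00 |
| Weeks 6-12 | 2 × 7 = 14 | 2 × 7 = 14 | 1.00 |
| After week 12 | 0 | 0 | n/a |
| Whole programme | 26 | 18 | 26/18 = 1.44 |
| With the three common visits | 29 | 21 | 29/21 = 1.38 |

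The three-fold imbalance belongs to weeks 2 to 5 only.

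**2. Illustration of the effect on recorded events, with equal true risk in both arms**

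P(recorded) = 1 − (1 − d)^k × (1 − q)

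- k: supervised sessions while the event is present.
- d: probability that one session brings the event to light.
- q: probability that a route equal in both arms (common visit, questioning, spontaneous report) catches it.

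The article gives neither d nor q. Both are assumptions and are shown as ranges.

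*Events lasting under a week in weeks 2 to 5* (k = 3 in PR, k = 1 in UC). Example with d = 0.3 and q = 0: PR 1 − 0.7³ = 0.657, UC 0.300, ratio 0.657/0.300 = 2.19. With q = 0.5: PR 1 − 0.343 × 0.5 = 0.829, UC 1 − 0.7 × 0.5 = 0.650, ratio 1.27.

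| d | q = 0 | q = 0.5 | q = 0.9 |
|---|---|---|---|
| 0.1 | 2.71 | 1.16 | 1.02 |
| 0.3 | 2.19 | 1.27 | 1.04 |
| 0.5 | 1.75 | 1.25 | 1.04 |
| 0.8 | 1.24 | 1.11 | 1.02 |
| 1.0 | 1.00 | 1.00 | 1.00 |

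*Events that last to the end of week 5 but no further*, with onset spread evenly over the four weeks (k = 12, 9, 6, 3 in PR and 4, 3, 2, 1 in UC). With q = 0 the ratio is 2.29, 1.57, 1.26 and 1.06 for d = 0.1, 0.3, 0.5 and 0.8. With q = 0.5 it is 1.24, 1.20, 1.11 and 1.03.

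*Events that persist through weeks 6 to 12* (14 further sessions in each arm). With q = 0 the ratio is 1.08 at d = 0.1 and 1.00 from d = 0.3 upwards.

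Wherever detection is imperfect and the event is short, the ratio is above 1, so the direction is against PR. The size falls quickly once an equal route works or the event lasts into the equal-contact weeks.

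**The case against.** The strongest reply is that physiotherapists are not the only route. Outcome measures/variables provides for monitoring of every patient throughout the study and accepts questioning and spontaneous report, neither of which needs a treatment session. A UC patient seen weekly may also recall last week's event. This stands, and it limits the point. A reader might infer that AEs reach the trial mainly through physiotherapists, so that counts follow contact and not risk. The article does not rank the routes, and recorded counts would reflect both. A reader might also carry the 3:1 session ratio over to a three-fold excess of events. That would require the sessions to be the sole route with very low detection at each one, which conflicts with the second route.

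Further points that stand:

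- Re-tear, the event in the stopping rule, is sought by ultrasound at 6 weeks and does not depend on session frequency.
- A reader might see bias from the lack of trial physiotherapy after week 12. That gap is equal in both arms, the 12-month visit remains, and treatment of AEs continues to week 52. It can cause under-recording but no imbalance in scheduled contact.
- The article condenses a fuller protocol and its assessment schedule figure is not shown. It cannot be said that no common AE query exists.
- The article does not say that complications are drawn from physiotherapist reports.
- Session frequency is part of the PR programme, so some extra events may be genuine. Equal true risk is assumed only to isolate ascertainment.

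These replies do not remove the imbalance. Even if a common query exists, a count that pools its yield with physiotherapist reports keeps the unequal component. The possibility of genuine extra events is itself a reason to compare the arms on equally collected data.

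**Conclusion.** The point holds in a limited form. AE ascertainment in weeks 2 to 5 is unequal by design, with 12 supervised sessions in PR and 4 in UC, and one named group of AE reporters works through those sessions. The resulting bias is confined to transient, non-serious events and runs against PR. With equal true risk, and per-session detection between 0.1 and 0.8, the PR:UC ratio of recorded events lasting under a week is about 1.2 to 2.7 if physiotherapists are the only route. It is 1.1 to 1.3 if an equal route catches half of events, 1.02 to 1.04 if that route catches nine in ten, and 1.00 to 1.08 for events that persist into weeks 6 to 12. These are illustrations; the article fixes neither probability. The primary outcome, the re-tear comparison and the stopping rule are not affected. The change is worth making because it is cheap and improves the between-arm safety comparison.

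**What to change.** 1. Base the between-arm comparison of AEs and complications on one structured query with the same wording and recall window in both arms, asked at the existing 6-week, 12-week and 12-month visits.
2. List physiotherapist-reported events separately, by source, and do not pool them into that comparison.
3. Report AEs for weeks 0-6, 6-12 and 12-52 separately, so that periods of dense and sparse contact are not merged.
4. Reconcile Outcome measures/variables with Safety monitoring on who elicits AEs and when. If the full protocol already contains a common query, cite it and name it as the source for the comparison.

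The cost is a short extra page in the existing web survey at three visits. Some brief events will be forgotten by the visit in both arms, but they still appear in the physiotherapist listing if reported there. Treatment and session schedules need no change.

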The Patient Global Rating Scale (GRS) is used to obtain a global/general impression of recovery from baseline to 6, 12 and 52 weeks postoperatively with the question: “Compared to when this treatment first started (before surgery), how would you describe your shoulder this last week?” This is assessed on a 15-point scale where − 7 represents vastly worse, 0 represents unchanged, and + 7 represents much better [57–59].

Patients are also asked about perceived pain using a NPRS [60, 61] with three questions: “On a scale from 0-10, where 0 equals no pain and 10 the worst imaginable pain, how much pain do you feel in your shoulder during resting? / How much pain do you feel in your shoulder during activity? / What is the maximal shoulder pain you have experienced within the past 24 hours?”

Further, patients are asked to report use of analgesics (type (paracetamol or opioids)/amount). Secondary clinical outcomes consist of active and passive shoulder elevation ROM in the scapular plane (standing); external and internal shoulder rotation (in 90° abduction when supine) [62, 63], as measured by digital inclinometer (Baseline Evaluation Instruments, model 12–1057 from Procare). Maximum voluntary isometric contraction (MVC) of shoulder external and internal rotation (sitting) and elevation in the scapular plane [62, 64, 65] is measured by dynamometer (IsoForceControl, model EVO2, 10-400 N, Medical Device Solutions AG). Furthermore, intraoperative information (including details of tendon repair) and patient-reported number of sick-leave days from work/time until return to work and leisure activities are registered.

Tendon healing characteristics of the repaired supraspinatus tendon (SST) and the subacromial space (SAS) are investigated at 12 months follow-up using US greyscale. The SAS and the SST thickness are also potentially important factors in understanding the pathogenesis of rotator cuff pathology [66, 67], tendinopathy [68] and ruptures [69] a year after repair [70]. Furthermore, power Doppler (PD) US is used for measuring vascularization as a sign of pathology and healing [70, 71]. The US examination is performed by the principal investigator ([name]) using a Hitachi Ascendus scanner and Hitachi Medical Systems Linear standard probe type L75 18–5 MHz 50-mm transducer (Hitachi Aloka Medical) and the musculoskeletal program. The depth preset is 2.50 cm and focus is adjusted, so it is placed right under the tendon.

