### Data collection

The primary investigator performs all enrollment after screening by the orthopedic surgeons. The primary investigator and two outcome assessors perform all baseline and follow-up assessments. Before starting the data collection, the assessors and the primary investigator decide on a consensus standard for collection and recording of all outcome variables. We use the Procordo Research Platform, which is an electronic online data trial management system (DTMS) (www.procordo.com) to collect and store the data. In the system the patients answer the questionnaires in a web-based survey form, and the outcome assessor manually registers data from the objective assessments. The DTMS includes automatic range checks of the entered data values, and the user will be alerted if the entered data fall outside a pre-specified range.

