### Blinding

Orthopedic surgeons will perform initial screening. As this is an “open-label” trial the health professionals delivering the interventions and the patients will not be blinded to treatment allocation. The principal investigator and outcome assessors will be blinded to treatment allocation during all pre-examinations and post-examinations, and patients are requested not to disclose their allocation when outcomes are assessed at weeks 6 and 12 and 12 months postoperatively. To test the efficacy of blinding, the outcome assessors are asked what treatment strategy they think a patient has received after assessments at week 12 postoperatively. The principal investigator and outcome assessors can be un-blinded if deemed necessary, e.g. in the case of (serious) adverse events that require these otherwise blinded persons to be involved in the solution of the event.

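### Adverse event reports from unblinded physiotherapists go to a blinded assessor, which puts assessor blinding at risk selectively in patients with events, mainly early ones

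*Protocol article*

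**What the plan says.** All references are to the protocol article.

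- **Who knows the arm.** Under Blinding, "the health professionals delivering the interventions and the patients will not be blinded to treatment allocation".
- **Who receives the reports.** Under Safety monitoring, "The physiotherapists at each center will report any adverse event to the primary investigator, who reports these to the ethics committee". Extreme worsening during exercise therapy that persists to the next session goes to the same person, who may refer the patient to a specialist.
- **Who judges relatedness.** Under Outcome measures/variables, "The investigator assesses and records any AE", and the record includes the "relationship of the AE to study intervention and any action(s) taken".
- **Who assesses outcomes.** Under Data collection, "The primary investigator and two outcome assessors perform all baseline and follow-up assessments". For the 12-month tendon measures, Outcome measures/variables says: "The US examination is performed by the principal investigator".
- **What is claimed.** Under Blinding, "The principal investigator and outcome assessors will be blinded to treatment allocation during all pre-examinations and post-examinations". The same section adds: "The principal investigator and outcome assessors can be un-blinded if deemed necessary, e.g. in the case of (serious) adverse events". It does not say who assesses the patient after such an unblinding.

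**The concern.** Patients and therapists are open-label, so blinded assessment is the main protection against measurement bias for outcomes that an examiner measures. The reporting line connects the people who know the arm directly to one of the people who should not. It operates only when a patient has an event, so any loss of blinding would fall on patients with pain or tendon problems, and more often in whichever arm has more events.

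The outcomes at stake are range of motion, isometric strength, and the ultrasound measures: tendon thickness, acromiohumeral distance and neovascularity. The Abstract lists all three groups as secondary outcomes. The WORC is completed by patients in a web form, so this route does not touch it directly.

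**Working it through.** No calculation of bias is possible, because the article gives neither an event rate nor an unblinding rate. The check sets the sections side by side.

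1. **Is it one person?** Patients and settings gives final eligibility and consent to the principal investigator. Data collection gives all enrollment to the primary investigator. Both describe the same task, so the two titles appear to mean one person. That person receives the reports, is a blinded assessor and is the ultrasound examiner.

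2. **Can a report reveal the arm without naming it?** Interventions and Table 1 give the contrast:
   - Weeks 2 to 5, exercise type: only progressive rehabilitation includes assisted active and active exercise. Usual care starts these in week 6.
   - Weeks 2 to 5, supervised sessions: 3 per week × 4 weeks = 12 under progressive rehabilitation, against 1 × 4 = 4 under usual care.
   - Mean spacing of sessions: 7/3 ≈ 2.3 days against 7 days. The worsening report depends on symptoms lasting to the next session, so its timing also differs by arm.
   - Weeks 6 to 12: both arms have the same supervised exercise, twice a week.

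   An event described as arising during an active exercise in week 3 points to progressive rehabilitation. After week 5 the content of a report no longer separates the arms. After week 12 rehabilitation moves to community providers who are not told the allocation.

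3. **Does the relatedness judgement add to this?** It is hard to judge whether an event relates to the intervention without knowing what the patient was doing. The text assigns the judgement to the investigator, without specifying the principal investigator.

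4. **Do the stated safeguards cover this route?**
   - Patients are asked not to disclose their allocation. No such request to therapists is stated.
   - Event-driven unblinding is allowed, but no change of assessor follows from it.
   - The blinding check is put to the outcome assessors after week 12. The Blinding section names them separately from the principal investigator, so the most exposed person may not be covered, and the 12-month ultrasound is not.
   - The person responsible for randomization watches the stopping threshold, but the reports still go to the primary investigator.

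**The case against.** The strongest reply is that nothing in the article says blinding is lost. The principal investigator stays blinded by default, unblinding is reserved for cases of need, and no sentence says that a report carries the allocation. This stands. A reader might infer that the blinding claim fails, or that the secondary outcomes are biased. The text supports only a risk.

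Other replies also narrow the point:

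- Relatedness is not expressly given to the principal investigator. This stands, but the reporting line alone creates the conflict.
- Report content reveals the arm mainly in weeks 2 to 5. This stands and limits the risk to early events.
- No frequency is given, and Safety monitoring expects few events. A reader might assume that 10 to 25% of the 100 patients have a reported event and conclude that 10 to 25 are unblinded. That range has no basis in the article, and it counts every event at any time as revealing the arm.
- A journal article leaves report forms and assessor rosters to fuller documents, and the figure listing responsible personnel is not available. This stands for those details. The reporting line and the three roles, however, are stated text, not omissions.
- An inclinometer, a dynamometer and measured ultrasound distances limit examiner discretion. They reduce it without removing it.

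**Conclusion.** The point holds as a conflict of roles. Reports from unblinded therapists go to a declared blinded assessor who is also the 12-month ultrasound examiner. In weeks 2 to 5 their content can reveal the arm, so blinding is at risk selectively in patients with events, mainly early ones.

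The size is unknown. For scale only, each percentage point of the 100 planned patients with an arm-revealing report is one patient. The risk concerns range of motion, strength and ultrasound, not directly the primary outcome. Ultrasound is the most exposed, because one named person performs it.

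The conclusion rests on two assumptions: that primary and principal investigator are the same person, and that a therapist's account of an event usually mentions the exercise or the session at which it arose. It does not require that the principal investigator judges relatedness, nor does it show that blinding fails in any patient.

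**What to change.** **Safety monitoring.** Name a recipient for adverse event and worsening reports, and a judge of relatedness, who assess no outcomes. Existing personnel would do: for example, the person responsible for randomization, who already monitors the adverse event count, could receive the reports, and a site orthopedic surgeon could judge relatedness. The clinical referral of patients should stay as it is. If the principal investigator learns an arm through a referral, the rules below apply.

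**Blinding.** Add three statements:

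- When a patient's arm becomes known to the principal investigator, one of the two other blinded assessors does that patient's later range of motion and strength assessments.
- Each unblinding is logged and reported by arm.
- The blinding check also covers the principal investigator, including at the 12-month ultrasound.

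**Analysis.** Keep all patients in the main ultrasound analysis. Any repeat without the unblinded patients should be labelled exploratory, because it excludes patients on a post-randomization event that may be linked to both arm and tendon outcome.

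The cost is a little coordination with staff already in the trial. Trial status says recruitment was still open at submission, so later assessments could still benefit.
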